## Abstract

**Background:**

Although a high intake of plant foods is often considered healthy, some plant foods can be detrimental to health. Reliable dietary assessment is crucial to examine the relationship between diet and disease. Current dietary assessment methods rely on self-reported intake data, which are subject to bias. Objective measurement using biomarkers of food intake could mitigate this problem. However, single biomarkers of food intake have limitations as well. Combining several biomarkers of food intake into a multibiomarker panel could attenuate these limitations and allow for an accurate, objective dietary assessment.

**Objective:**

The PLAENTI study aims to validate a multibiomarker panel for the assessment of quantity and quality of plant foods in the diet.

**Methods:**

PLAENTI is a randomized controlled trial with 4 arms in a parallel design. Metabolically healthy adults (≥18 years old) were enrolled in the study. The study consisted of 1 week of run-in, with a standardized diet low in healthful plant foods for all participants; 2 weeks of a dietary intervention according to the assigned arm; and 1 week of washout, during which participants returned to their habitual diet. During the intervention, the participants’ diet consisted of either a low, medium, or high proportion of healthful plant foods or a high proportion of unhealthful plant foods in the diet according to the assigned arm. The arm that received a high proportion of healthful plant foods served as the control. All food was provided based on energy-adjusted menu plans. During the visits, anthropometry and body composition were assessed, and blood samples were collected. Throughout the study, participants collected multiple urine samples (24-hour urine, evening and morning spot urine) and stool samples. Blood and urine samples will be analyzed by liquid chromatography-mass spectrometry to determine biomarker levels for the validation of a multibiomarker panel.

**Results:**

After receiving approval from the ethics committee, recruitment began, and the first screening visit took place in November 2023. Between January and August 2024, of the 66 enrolled participants, 59 (31 female, 28 male) successfully completed the study, and their urine, blood, and stool samples are available for analysis. PLAENTI was conducted in 5 waves with a maximum of 16 participants enrolled in each wave. The mean age of the study population was 45.5 (SD 18.4) years, the mean BMI was 24.8 (SD-3.9) kg/m², and the mean total energy expenditure was 2464 (SD 440) kcal.

**Conclusions:**

PLAENTI was conducted in a highly controlled and standardized manner, yielding samples and data that will be used to examine whether the quantity and quality of plant foods in the diet can be assessed using a multibiomarker panel. Successful validation of the multibiomarker panel would enable its application for objective dietary assessment.

## Introduction

A high intake of plant foods within a diet is often considered healthy. However, there are also plant foods that can be detrimental to health. For this reason, plant-based diet indices have been developed, which distinguish between “healthful” and “unhealthful” plant foods and form 3 categories: a general plant-based diet index, a healthful plant-based diet index, and an unhealthful plant-based diet index [1,2]. This distinction between healthful (eg, whole grains, unprocessed fruits and vegetables, nuts, and seeds) and unhealthful (eg, refined grains, sugar-sweetened beverages, and unfavorable vegetable oils) plant foods made it possible to obtain more detailed data on the relationship between diet and disease [1,2]. To date, nutritional epidemiology has relied on self-reported intake data, collected by tools such as food frequency questionnaires (FFQs), 24-hour recalls, and weighed or estimated diet records, which are prone to bias [3-6]. Self-reported data are subjective and influenced by factors such as the social desirability of food items, how individuals estimate portion sizes, the training of subjects, and the interview itself [3,7]. Well-known inaccuracies of plant food assessment include overreporting of fruit and vegetable intake and underreporting of oil and nut consumption [8-11]. The reliability of data may be enhanced by repeated measurements, improvement of assessment tools, or country-specific adaptation [7,12]. On the other hand, repeated measurements or higher-validity tools, such as 7-day dietary records, will increase the burden on participants [12].

There is growing evidence that biomarkers of food intake (BFIs) are a valuable tool for improving the accuracy of dietary assessment by introducing objective measurement [6,13-17]. However, BFIs also have limitations. There are overlaps between different foods with the same biomarker, and only a few food-specific biomarkers are known. Additionally, the concentration of some BFIs in biospecimens can vary between individuals, depending on factors such as age, sex, physical activity, and body composition [18]. Validation of candidate BFIs is of key importance and still scarce [15,19]. Combining several biomarkers into a multibiomarker panel (MBP) may mitigate the limitations of single BFIs and self-reported intake data [13,20]. It has been shown to increase the specificity and robustness of dietary assessment for individual foods (eg, banana, cocoa, and walnut) and for food groups such as total fruit intake [21-24]. However, dietary patterns, rather than individual nutrients or foods, have become a prominent topic in epidemiology, and several associations have been discovered between dietary patterns and noncommunicable diseases [25-28]. To apply BFIs and MBPs in epidemiological research, it is necessary to study and validate BFIs for the habitual diets of individuals or dietary patterns within populations. Accordingly, MBPs that include specific BFIs, BFIs for food groups, and BFIs that overlap between several food items could be promising to cover dietary patterns [29-34].

Cuparencu et al [35] recently reviewed validation criteria for BFIs and the general concepts of objective dietary assessment and listed known BFI candidates and their utility levels, as well as potential MBPs. The review also proposes research gaps. These include the identification of new MBPs and the discrimination of, for example, animal versus plant foods or healthful versus unhealthful foods. Additionally, more data on the interplay between BFI kinetics, frequency of food consumption, sampling schemes, sampling time windows, and different biospecimens are needed [35]. Furthermore, most studies still focus on biomarker discovery, often with untargeted analytical methods [33,36]. Beckmann et al [37] measured an MBP consisting of 54 BFI candidates in the urine samples of 15 participants who received a 3-day menu plan. The researchers were able to discriminate between the 3 dietary patterns that mimicked common UK diets [37]. Ultimately, more research is needed to unlock the full potential of BFIs and MBPs. Intervention studies specifically designed to measure BFIs in various samples from a diverse group of individuals consuming exact amounts and types of food, while considering dose- and time-response aspects, are necessary.

The JPI HDHL–funded project Plant*Intake* (acronym for “Combining biomarker panels and dietary intake data for improved assessment of healthful/unhealthful plant food intake”) aims to adapt the plant-based diet indices described by Satija et al [1] to better fit to European diets and common foods (European plant-based diet indices). Furthermore, an MBP reflecting the quantity and nutritional quality (healthful vs unhealthful) of plant foods in the diet will be derived using intake data and samples from previous studies. Validation of MBPs is paramount for future use. Therefore, the developed MBP will be validated with data from the intervention study PLAENTI (“Validating a multibiomarker panel for the assessment of quantity and quality of plant foods in the diet”), which is described in this study protocol.

The aim of the PLAENTI study is to validate an MBP for the assessment of the quantity and nutritional quality of plant foods in an omnivorous diet. Accordingly, the primary objective of the validation study PLAENTI is to test whether the quantity of plant foods within the diet can be correctly estimated by measuring levels of selected urinary and blood biomarkers that are part of the MBP. A secondary objective is to test whether a difference in nutritional quality (healthful vs unhealthful) of plant foods in the diet can also be detected with the MBP. The effect of potential confounders (age, sex, physical activity, and body composition) on the precision of estimating plant food intake using the MBP will be assessed. Finally, the MBP will be determined in both 24-hour urine and spot urine samples. This will allow a comparison of the different sample types (24-hour urine collection, evening and morning spot urine, and different pools of these spot urines) to assess their reliability in reflecting dietary patterns through biomarker analysis. To address these objectives, participants received a 2-week dietary intervention with different proportions and nutritional qualities of plant foods, while urine and blood samples were collected at several time points.

## Methods

### Study Design

The PLAENTI study was conducted at the Study Center for Human Nutrition of the Max Rubner-Institut, Federal Research Institute of Nutrition and Food in Karlsruhe, Germany, from January 9 to August 15, 2024. PLAENTI was designed as a randomized controlled trial with 4 arms. A parallel-group design was chosen to efficiently conduct the study and allow for direct comparison of results between the arms. A total of 66 participants were enrolled and randomized to 1 of 4 arms, stratified by sex. For logistic reasons, the study was conducted in 5 waves, each with a maximum of 16 participants. Each wave lasted a total of 4 weeks and started with a 1-week run-in period during which all participants consumed the same diet consisting of a low proportion of healthful plant foods to achieve comparable baseline levels of biomarkers. For the 2-week intervention period, participants were assigned to 1 of 4 interventions and received a diet that varied in the quantity and nutritional quality of plant foods to mimic different dietary patterns. The intervention was followed by a 1-week washout period, during which the participants returned to their habitual diet.

The study was carried out in an outpatient setting. Participants collected urine and stool samples and prepared and consumed food at home. Visits to the study center took place once a week on an identical schedule for all participants. Participants were asked to fast for at least 10 hours beforehand and underwent a series of standardized examinations and measurements described in detail below. Standard operating procedures were developed and tested for feasibility for all interviews, examinations, measurements, sample collections, sample preparations, and storage. Interviewers and examiners were extensively trained before and supervised during data collection. An overview of the study procedure is shown in Figure 1.

**Figure 1. F1:**
[figure not shown]
Overview of the study procedure. The figure shows the time sequence of run-in, intervention (either low, medium, or high in healthful or high in unhealthful plant foods), and washout, with corresponding visits to the study center and sample collections at home, as well as the schedule of visits to the study center and deliveries (A, B, and C). BIA: bioelectrical impedance analysis; FFQ: food frequency questionnaire; GI questionnaire: gastrointestinal symptom questionnaire.

Prior to PLAENTI, an internal feasibility study called prePLAENTI was conducted (unpublished; registered at the German Clinical Trials Register: DRKS00031484, available at [38]). The purpose of prePLAENTI was to evaluate the acceptability of the standardized diets for participants and the feasibility of the planned study procedures. Participant feedback and process evaluation by the study center were used to ensure that PLAENTI can be conducted efficiently.

### Recruitment

Female and male volunteers aged 18 years or older were eligible to participate. Detailed inclusion and exclusion criteria are listed in Textbox 1. Medical history was obtained using a health status questionnaire, and a basic physical examination was performed.

Textbox 1.Eligibility criteria of the PLAENTI study*.*
**Inclusion criteria**
Females and males, 18 years or olderVolunteers who are able to comply with the study termsParameters of liver and kidney function, carbohydrate and lipid metabolism, showing no pathological significanceNonsmokersOmnivorous dietWritten informed consent to participate in the study
**Exclusion criteria**
Diseases affecting the absorption, digestion, metabolism, or excretion of nutrientsAcute or chronic infectious diseasesTumors requiring therapyHistory of bariatric surgeryHistory of gastrointestinal tract surgery affecting the absorption, digestion, metabolism, or excretion of nutrientsHistory of pancreas surgeryCholecystectomyAcute or regular intake of medications resulting in energy or nutrient malabsorptionAllergy or intolerance to any food or food ingredient in the study dietUse of dietary supplements <2 weeks prior to the study periodUse of antibiotics <3 months prior to the study periodBlood donation during or <4 weeks prior to the study periodPregnancy and breastfeedingIllegal drug useAlcohol or drug abuseParticipation in other clinical trials that may affect the outcome of this studyIndividuals living in a care facilityIndividuals deprived of their liberty by a court or administrative orderIndividuals who are not expected to comply with the terms of the study

Participants were recruited in Karlsruhe, Germany, and the surrounding area. Posters and flyers were distributed at local and regional universities and public institutions (eg, libraries), doctors’ offices, pharmacies, and health care facilities. In addition, recruitment was carried out via local/regional print media and social media in accordance with the requirements of the “Social Media Guideline” [39]. In addition, invitation emails were sent to potentially eligible participants listed in the study center’s participant database to inform them about the study. First, persons interested in study participation were informed about the nature and scope of the trial in a detailed telephone screening. Then, potential participants were asked to visit the study center for a screening that included basic physical examinations and a detailed information session.

### Allocation

The allocation sequence was generated by a biostatistician who was not involved in any further steps during the ongoing study and had no direct contact with the participants. Participants were randomly assigned to 1 of the 4 intervention arms with a 1:1:1:1 allocation by repeatedly using the “sample” function of the R software (R Core Team). Specifically, cluster randomization was used with clusters of different sizes. The clusters were heterosexual couples on the one hand and individual persons on the other. We randomized within waves for logistic reasons and stratified by sex to assess effects for females and males independently. The result of randomization was a sequential list of intervention arms with the corresponding study identifier of participants. The randomization plan is reproducible.

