#### Sample Size

The MBP to be validated in this study will be developed at a later stage of the Plant*Intake* project, so it was not possible to calculate the sample size prior to submission of the project proposal. As a Williams test is performed in the main statistical analysis, this was used as the basis for a sensitivity analysis. The calculation was performed using the R package “MCPAN” (R version 4.1.0, R Core Team). The option “Type: Williams” was used. Specifically, for a 3-arm design (for the primary outcome) with n=15 per arm and expected values for the MBP of 1 (LH), 2 (MH), and 3.8 (HH), and a homoscedastic variance of 2.5, a power of 0.81 was obtained [21,44-46]. A total of 60 participants were expected to complete the study, with even distribution between the groups.

Based on experience with previous studies, including a study with low, medium, and high intake of fruits and vegetables by Watzl et al [47] and the more recent JPI FoodBAll study (Universal Trial Number: U1111-1177-1536), a dropout rate of 12% was assumed. Therefore, in order to analyze a total of 60 participants, the goal was to enroll 68 participants in total.

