#### Statistical Methods

The aim of the primary statistical analysis is to detect a trend in the MBP as a function of the proportion of healthful plant foods consumed by the participants. Here, the values of the MBP determined at visit 4 are adjusted with the baseline values from visit 2. The MBP values are compared between the interventions using the Williams test. The comparison is made for the 3 diets with different proportions of healthful plant foods (low, medium, or high). For simplicity, it is assumed that the primary outcome is normally distributed and has a homogeneous variance. The statistical hypothesis is that the primary outcome will follow a trend for the ordered categories of low, medium, and high intake of healthful plant foods. Group HH, with a high proportion of healthful plant foods in the diet, serves as a control. The following 3 average values of the MBP are assumed for the 3 intervention groups: *μ*1*, μ*2*,* and *μ*3. All intervention groups have a comparable sample size. An average different response is expected in the group with low and medium consumption compared to the high consumption (control) of healthful plant foods. The global null hypothesis is formulated as *H*0*: μ*1*=μ*2*=μ*3 versus the alternative hypothesis *H*1*: μ*3*≥μ*2*≥μ*1, with at least one strict inequality. When modeling the MBP, adjustment is made for the following potential confounding variables: age, sex, body composition (assessed by BIA), and physical activity (assessed by accelerometry). The MBP is considered to be validated if a significant monotonic trend is observed (*P*<.05).

As the main secondary analysis, mean MBP values will be compared between the HH and HU intervention arms, characterized by similar proportions of plant foods but differing in nutritional quality (healthful vs unhealthful). Group differences will first be assessed using an independent-samples *t* test, followed by linear regression models incorporating the same set of adjusting variables.

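### Couples were randomised as clusters, but the named analyses and the power figure treat all participants as independent; if partners' outcomes are positively correlated, the validation test can reject too often

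*Protocol article*

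**What the plan says.** **Unit of randomisation.** The Allocation section gives a 1:1:1:1 allocation to four arms, made within waves and stratified by sex, and adds that "cluster randomization was used with clusters of different sizes. The clusters were heterosexual couples on the one hand and individual persons on the other". Both partners of a couple therefore share an arm.

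**Primary analysis.** Under Statistical Methods, "The MBP values are compared between the interventions using the Williams test", for the low (LH), medium (MH) and high (HH) healthful plant food arms. On the error distribution the article says only that "it is assumed that the primary outcome is normally distributed and has a homogeneous variance". The covariates are age, sex, body composition and physical activity. A significant monotonic trend at P<.05 counts as validation of the panel.

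**Secondary analysis, HH against HU** (high in unhealthful plant foods). "Group differences will first be assessed using an independent-samples" t test, "followed by linear regression models incorporating the same set of adjusting variables".

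**Power.** The Sample Size section bases its figure on the Williams test "for a 3-arm design (for the primary outcome) with n=15 per arm" and obtains 0.81.

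None of these contains a couple term, a cluster-robust variance or a design effect. The number of couples is not reported.

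**The concern.** When two people are allocated as one unit, they supply two independent observations only if their outcomes are uncorrelated given arm and covariates. If they are positively correlated, the variance of an arm mean is larger than an analysis of independent individuals assumes, and its standard errors are too small.

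A positive correlation is plausible. Meals were prepared and eaten at home. Coffee, tea and the extra snack were partly at the participant's discretion, and the article classes coffee and tea as healthful plant foods. Compliance was not measured objectively. Partners could resemble each other in all of these.

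The validation claim rests on a single P value, so the type I error of that test is the property at stake. If the clustering is handled correctly, power falls below the stated figure.

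**Working it through.** **1. The plan's own figure.** Inputs from Sample Size: 15 per arm, means 1, 2 and 3.8, spread 2.5. With 45 independent observations the residual df are 3 × 15 − 3 = 42. A Williams-type multiple contrast test (two-sided 5% critical value about 2.19, LH as reference, SD 2.5) gives a power of 0.814, which matches 0.81. With HH as reference it is 0.845. Reading 2.5 as a variance gives more than 0.99. That discrepancy is a separate matter. Here the point is that 0.81 is reached with 45 independent people and no allowance for couples.

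**2. Design effect.** Let an arm of n people contain c couples and n − 2c singles, with f = 2c/n.

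- Sum of squared cluster sizes over sum of sizes = (4c + n − 2c)/n = 1 + f.
- Design effect DE = 1 + f × ICC. The correct standard error is the naive one times sqrt(DE).
- Example: 4 couples in 15 gives f = 8/15 = 0.533. With ICC 0.3, DE = 1 + 0.533 × 0.3 = 1.160 and sqrt(DE) = 1.077.

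**3. What the documents say about f.** Only a ceiling follows from the completers by sex in Table 2 (LH 7F/7M, MH 9F/6M, HH 8F/7M, HU 7F/8M). The three primary arms can hold at most 7 + 6 + 7 = 20 complete couples, that is 40 of 44 people (f ≤ 0.91). HH and HU together can hold at most 14 couples, 28 of 30 people (f ≤ 0.93). There is no lower bound, and nothing is given on the ICC. Both are assumed below.

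**4. Type I error of the unadjusted Williams test.** Simulation under equal means: 3 arms of 15, pooled variance, contrasts with HH as base, two-sided critical value 2.195, 400,000 replicates per row.

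| Couples per arm (f) | ICC | DE | sqrt(DE) | Type I error |
|---|---|---|---|---|
| 1 (0.13) | 0.1 | 1.013 | 1.007 | 5.2% |
| 1 | 0.3 | 1.040 | 1.020 | 5.6% |
| 1 | 0.5 | 1.067 | 1.033 | 5.9% |
| 2 (0.27) | 0.1 | 1.027 | 1.013 | 5.3% |
| 2 | 0.3 | 1.080 | 1.039 | 6.1% |
| 2 | 0.5 | 1.133 | 1.065 | 6.8% |
| 4 (0.53) | 0.1 | 1.053 | 1.026 | 5.8% |
| 4 | 0.3 | 1.160 | 1.077 | 7.2% |
| 4 | 0.5 | 1.267 | 1.125 | 8.8% |
| 6 (0.80) | 0.1 | 1.080 | 1.039 | 6.1% |
| 6 | 0.3 | 1.240 | 1.114 | 8.4% |
| 6 | 0.5 | 1.400 | 1.183 | 10.9% |

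The article does not state sidedness. One-sided, the rates for 2, 4 and 6 couples at ICC 0.3 to 0.5 are 5.9 to 6.3%, 6.6 to 7.7% and 7.5 to 9.1%. A two-arm t test of the HH–HU kind gives 5.9 to 6.6%, 7.0 to 8.2% and 8.0 to 10.3%.

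**5. Power once clustering is respected** (the variant that reproduces 0.81, standard error multiplied by sqrt(DE)):

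- f = 0.10, ICC 0.1: DE 1.010, power 0.81
- f = 0.25, ICC 0.3: DE 1.075, power 0.79
- f = 0.50, ICC 0.3: DE 1.150, power 0.75
- f = 0.50, ICC 0.5: DE 1.250, power 0.72

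**6. A force in the other direction.** Randomisation was within five waves, and wave is not among the listed covariates. Wave variance that is balanced across arms but left in the residual makes the test conservative. With arms balanced over waves and assumed wave shares of 0, 10 and 20% of the variance, type I error at ICC 0.3 is 6.1, 5.1 and 3.9% with 2 couples per arm, and 7.1, 5.8 and 4.9% with 4. With 5 couples, ICC 0.5 and a wave share of 10%, it is still 8.3%.

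**The case against.** The strongest reply is that neither ingredient of the problem is documented. Couples may have been few, and the residual correlation may be small. The outcome is a change from visit 2 to visit 4 after a common run-in diet, which removes much of any stable difference between couples. Age and physical activity, which partners may share, are covariates. Portions were scaled to each person. Partners are of opposite sex, so in the unadjusted t test a sex effect lowers their correlation. Unmodelled wave variance works against inflation, as step 6 shows. Finally, this is a condensed article whose analysis plan is not shown, and that plan may hold the error structure of the model.

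Much of this stands. A reader might infer that the standard errors are too small as a matter of fact, or that partners cooked in one kitchen and shared storage. The documents do not support either: they give no couple count and no correlation, and they do not say that couples lived or cooked together. Shared food batches are not specific to couples either, since the study center supplied everyone. A reader might also want household added to the urine-sample mixed models. Sample type and time vary within participant there, and the participant random effect already absorbs couple-level variance for those contrasts, so little would change.

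What does not stand is that the matter is merely left open. The article itself names an independent-samples test for data it describes as cluster-randomised, lists the adjusting variables without couple, and reports a power that reproduces only with independent people. An offset of unknown size from leaving out wave does not repair the omission of couple.

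**Conclusion.** The mismatch between the randomisation unit and the named analyses is established from the article's own text. Its consequence is conditional. If within-couple correlation after adjustment is positive, the true standard errors exceed the reported ones by the factor sqrt(1 + f × ICC). Before any offset from wave variance, type I error is about 5.2 to 6.1% with one couple per arm or an ICC of 0.1, and about 6 to 11% with 2 to 6 couples per arm and an ICC of 0.3 to 0.5. Power falls from 0.81 to between 0.79 and 0.72 for f of 0.25 to 0.5 and ICC of 0.3 to 0.5. All of these rest on assumed couple counts and ICCs. In the lightest cases the effect is negligible, and wave variance could cancel it. In the heavier ones the P<.05 validation rule is not a 5% test. The documents do not show which case applies.

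**What to change.** Take the Williams contrasts (LH, MH, HH) and the HH–HU contrast from a linear model that respects the randomisation unit. Use either a couple random intercept, with singles as clusters of one and Satterthwaite or Kenward-Roger df, or cluster-robust standard errors with a small-sample correction. Let this replace the plain t test. Report the number of couples per arm, and state that the 0.81 power assumes independent participants.

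The cost is a few sentences in the analysis plan and a couple identifier, which the randomisation already needed. The article describes the biomarker analysis as still to come, so the change can be fixed before results are known. The downsides are slightly wider intervals and, if couples are few, an imprecisely estimated couple variance.
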